### Research hypothesis

1.2

The utilization of an acclimatization visit of nitrous oxide sedation before commencement of treatment will result in improvement in child's behavior and reduction in the anxiety levels during dental treatment as measured by the salivary Amylase and Cortisol levels.

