### Primary outcome

2.1

Improvement in behavior and anxiety levels. The primary outcome measured by:

(1)Physiologically by measuring anxiety-related changes using salivary levels of Alpha Amylase and Cortisol.(2)Anxiety scores at baseline (initial visit) and after treatment (second visit) using a component from the indicator of sedation need (IOSN).(3)Behavior score will be recorded using, Frankl behavior rating scale (FBRS).

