**Figure 1 F1:**
[figure not shown]
Flowchart of the study design.

After baseline examination by the clinical team, eligibility verification, the primary investigator will obtain the participant's assent and parents’/guardian's consent submission (Appendix I, http://links.lww.com/MD/D198), participants will be randomized to either of the two study groups (30 patients per group). The study group will include families (children and parents) who would attend a visit for prevention where IHS will be introduced and tried while the control group will be the families who would attend for a prevention visit and discussion of IHS procedure only.

Block randomization with a 1:1 allocation will be performed. Concealment of allocation will be achieved by using identical, sealed, sequentially numbered, opaque envelopes that will contain group assignment. The envelopes will be opened sequentially by a dental assistant, only after the envelope has been irreversibly assigned to each participant and will remain unknown to the clinical team.

At the initial acclimatization visit, the sedation need score will be recorded using the pediatric indicator of sedation need (p-IOSN). Acclimatization visit will be carried out by a single pediatric dentist who will not be involved in the treatment of the patients. To be consistent, an information script will be prepared and rehearsed so that the same instructions about the IHS will be delivered to all participants. During the acclimatization visit, the pediatric dentist will record the p-IOSN score based on the answers of the participants to the components of the index. At the beginning of the visit, an unstimulated salivary sample of 1.5 to 2 ml will be collected to measure the levels of Alpha Amylase and Cortisol. For the intervention group only, a 15 minutes nitrous oxide IHS will be administered without any dental procedures performed.

During the second visit, two unstimulated 1.5 to 2 ml samples of saliva will be collected 15 minutes before the start of the procedure and 15 minutes after the conclusion of the procedure. The dental treatment for both study and control participants will include administering local analgesia and restoring decayed teeth with or without pulp therapy and/or dental extractions. The intervention will be carried out by a single pediatric dentist.

The 3 components of p-IOSN (Fig. 2, Tables 1 and 2) include:

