### Statistical analysis

2.8

Data analysis will be conducted, after investigating distribution normality, with the appropriate parametric or non-parametric statistical tests using the statistical software SPSS 24.0.0 (^©^SPSS Inc, Chicago, Ill). The level of significance will be set at *P* < .05. Use of Descriptive statistics and quantitative data will be analyzed using means and standard deviations if normally distributed or medians and interquartile range if skewed. Mean changes of anxiety scores and corresponding 95% confidence intervals will be determined to compare the two treatments (sedation with familiarization and sedation without familiarization). *T*-tests will be used to compare quantitative data if normally distributed or Mann–Whitney *U*-test if skewed. The Chi-square test will be used to investigate association of categorical data. Box plots, individual and mean profiles of anxiety scores at each assessment time point for each treatment will be produced.

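### The saliva primary outcome names neither its reference sample nor its outcome sample, and taking the visit-2 pre-procedure sample as baseline could shrink, erase or reverse a true benefit

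*Protocol article*

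**What the plan says.** Section 2.1 (Primary outcome) lists saliva first: "Physiologically by measuring anxiety-related changes using salivary levels of Alpha Amylase and Cortisol". It gives no start or end sample. The next item in the same list does fix its pair: "Anxiety scores at baseline (initial visit) and after treatment (second visit").

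The design text around Figure 1 (under 2.2) sets out the sampling:

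- Visit 1: "At the beginning of the visit, an unstimulated salivary sample of 1.5 to 2 ml will be collected".
- Later in visit 1: "For the intervention group only, a 15 minutes nitrous oxide IHS will be administered without any dental procedures performed".
- Visit 2: "two unstimulated 1.5 to 2 ml samples of saliva will be collected 15 minutes before the start of the procedure", and again 15 minutes after it ends. In context, the two samples are one before and one after.

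Section 1.2 states the hypothesis as a "reduction in the anxiety levels during dental treatment as measured by the salivary Amylase and Cortisol levels".

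Section 2.8 (Statistical analysis) mentions change only for the anxiety scores: "Mean changes of anxiety scores and corresponding 95% confidence intervals will be determined to compare the two treatments". Other quantitative data fall under the general rule that t-tests "will be used to compare quantitative data if normally distributed or Mann–Whitney" if skewed. It names no saliva contrast and no baseline adjustment.

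**The concern.** With three samples per child, the word used in 2.1 can mean visit 1 to visit-2 before, visit 1 to visit-2 after, or visit-2 before to visit-2 after. The last pair looks natural because the visit-2 samples bracket the procedure. But its first member is taken after randomisation and after one arm has had the acclimatisation sedation. If acclimatisation works partly by making children calmer on arrival, that calm is part of the treatment effect, and subtracting it takes that part away.

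Saliva is the measure named in the article's title and aim. If the pair is still open when results are known, the same data could support different conclusions according to the pair chosen.

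**Working it through.** **The plan's own figure.** Section 2.3 states 80% power with 30 patients but gives no effect size or SD, so the figure cannot be reproduced. It can only be inverted. With 30 per group and two-sided 0.05, the normal approximation gives (1.960 + 0.842) × √(2/30) = 0.72 SD; with the t distribution it is 0.736 SD. I use 0.74 SD as the assumed benefit, so that it matches the trial's size. (If 30 were the total, the implied difference would be 1.02 SD by the normal approximation. Section 2.3 also plans to recruit 40 per group, whereas the design text says 30 per group. Neither changes the argument.)

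**Assumptions, none from the documents.** Equal unit SD at every sample; two-sided 0.05; correlation ρ between any two samples of 0.3, 0.5 or 0.7; benefit of 0.74 SD at the post-procedure sample; a share f of that benefit already present at the visit-2 pre-procedure sample.

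**Change within visit 2.** Its expected contrast is the post-procedure effect minus the pre-procedure effect, 0.74 × (1 − f). Its SD is √(2(1 − ρ)). The standardised contrast is therefore 0.74(1 − f)/√(2(1 − ρ)). Multiplying by √(30/2) = 3.873 gives the noncentrality of a t-test on 58 df. At ρ = 0.5 the SD is 1, so f = 0 gives 0.74 × 3.873 = 2.87 and power 80.5%; f = 0.5 gives 0.37 × 3.873 = 1.43 and power 29%.

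| Share f present before | Contrast (SD) | Power, ρ = 0.3 | ρ = 0.5 | ρ = 0.7 |
|---|---|---|---|---|
| 0 | 0.74 | 66% | 80% | 95% |
| 25% | 0.56 | 43% | 56% | 78% |
| 50% | 0.37 | 22% | 29% | 44% |
| 75% | 0.19 | 9% | 11% | 15% |
| 100% | 0 | 2.5% each way | 2.5% each way | 2.5% each way |
| 150% | −0.37 | 22% against | 29% against | 44% against |

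The last row gives the chance of a significant result against acclimatisation although the true effect is a benefit at both visit-2 samples.

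**Visit-2 post-procedure value.** Compared without adjustment, the standardised contrast is 0.74 and power is 80%. Adjusted for the visit-1 value (ANCOVA), the residual SD is √(1 − ρ²), so the standardised contrast is:

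- ρ = 0.3: 0.74/√0.91 = 0.776, power 84%.
- ρ = 0.5: 0.74/√0.75 = 0.854, power 90%.
- ρ = 0.7: 0.74/√0.51 = 1.036, power 98%.

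The expected contrast stays at 0.74 SD whatever f is, because the visit-1 sample precedes the intervention.

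**The case against.** A reader might infer that the protocol has chosen the within-visit-2 change and will therefore lose or reverse the effect. The documents do not support that:

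- **No such analysis is stated.** No section says that the saliva outcome is the before-to-after difference at visit 2. Sections 1.1 and 1.2 speak of levels, and the assay description in the design text uses the word for changes in the sense of a bodily response indexed by levels. A plain comparison of visit-2 levels fits the text and is free of this problem.
- **Visit 1 is the evident baseline.** Section 2.1 equates baseline with the initial visit for the anxiety score, and the first saliva sample is taken then.
- **Erasure and reversal are special cases.** They need the effect before the procedure to equal or exceed the effect after it. A smaller share only shrinks the contrast. With no effect beforehand and correlation 0.7, the within-visit change has 95% power and does well. The documents give no size for any effect on arrival.
- **Reactivity is a possible question.** One reading of the hypothesis is stress response across the procedure, which the visit-2 change would address.
- **Model detail may sit elsewhere.** Log transformation and covariates are often left to an analysis plan, which is not shown.

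These points limit the claim to a risk. They do not remove it. Which samples define a primary outcome belongs in the outcome definition, and 2.1 makes that choice for the anxiety score but not for saliva. That several readings fit the text shows that the outcome is open. If reactivity were the intended question, that too would have to be stated, because it differs from the effect of acclimatisation on anxiety levels.

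**Conclusion.** The point holds as a gap in the definition of a primary outcome: neither the reference sample nor the outcome sample for saliva is named. Both visit-2 samples follow randomisation and the arm-specific sedation, so the visit-2 pre-procedure sample cannot serve as a neutral baseline. That follows from the design text alone.

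The size of the harm rests on assumptions. It ranges from none, if acclimatisation does nothing before the procedure, through a fall from about 80% to 29% power when half the effect is already present (correlation 0.5), to a contrast of zero or of the wrong sign when the earlier effect equals or exceeds the later one. Separately, the unadjusted tests in 2.8 make no use of the visit-1 value already collected; the gain forgone is about 4, 10 and 17 percentage points of power at correlations 0.3, 0.5 and 0.7.

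**What to change.** **Section 2.1.** State that the visit-1 sample is the saliva baseline. For each marker, name in advance one visit-2 sample as the primary time point and make the other secondary. Which one to choose is for the investigators, guided by the hypothesis; it has to be fixed before data are seen.

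**Section 2.8.** For saliva, replace the unadjusted t-test or Mann–Whitney test with a comparison of the visit-2 value adjusted for the visit-1 value (ANCOVA, on the log scale if skewed). Report the visit-2 before-to-after change as descriptive only.

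**Cost.** A sentence or two in each section. All three samples are already planned, so no extra visit, assay or child is needed.

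### The saliva samples bracket the treatment rather than measure anxiety during it, and the post-procedure value carries avoidable noise from an unstratified, unadjusted mix of treatments

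*Protocol article*

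**What the plan says.** The Research hypothesis (1.2) expects a "reduction in the anxiety levels during dental treatment as measured by the salivary Amylase and Cortisol levels". The Primary outcome (2.1) includes the salivary component: "Physiologically by measuring anxiety-related changes using salivary levels of Alpha Amylase and Cortisol".

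Sampling is described in the procedures text under 2.2, after Figure 1. At the first visit: "At the beginning of the visit, an unstimulated salivary sample of 1.5 to 2 ml will be collected". At the second visit, two samples are taken: "15 minutes before the start of the procedure and 15 minutes after the conclusion of the procedure". The treatment between those two samples, in both arms, consists of "administering local analgesia and restoring decayed teeth with or without pulp therapy and/or dental extractions".

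On allocation, the same text says "Block randomization with a 1:1 allocation will be performed" and names no stratification factor. Statistical analysis (2.8) compares quantitative data by t-test, or by Mann-Whitney test if skewed, and names no covariate. Treatment complexity is scored as a component of the p-IOSN at the initial visit, but no use of it in allocation or analysis is stated.

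**The concern.** There are two linked issues.

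**What the saliva result can support.** The hypothesis ties anxiety during treatment to saliva, yet no sample is taken during treatment. The earlier second-visit sample reflects anticipation. The later one is timed from the end of the procedure, so it follows the whole of whatever was done to that child. The Discussion offers the salivary result as evidence for guidelines, so the wording of the conclusion matters.

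**Precision of the later sample.** A child who has had an extraction and one who has had only restorations are sampled at the same interval after different stressors. If the type of treatment shifts amylase or cortisol, that shift is variance unrelated to acclimatization. It falls on a primary outcome in a trial of 30 to 40 children per arm, and neither the allocation nor the stated test removes it.

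**Working it through.** **Timing.** Set the hypothesis beside the sampling schedule. The three saliva samples are at the start of visit 1, 15 minutes before the visit-2 procedure and 15 minutes after it. None falls within treatment. This needs no arithmetic.

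**Inputs for the precision question**
- From the article: 80% power, 30 patients required, 40 recruited per group, dropout 20–30% (2.3); 30 per group (procedures text); significance level 0.05 (2.8).
- Assumed, because the article does not give them: a two-sided test; 30 analysed per arm; share of children with an extraction p = 0.3 to 0.5; shift in the marker after an extraction k = 0.5 to 1 SD. Thirty analysed is consistent with 2.3, since 40 × 0.8 = 32 and 40 × 0.7 = 28.

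**Step 1, the plan's own figure.** The 30 cannot be reproduced, because no effect size or SD is stated. Solving backwards with the normal formula for two means:

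d = (1.960 + 0.842) × √(2/30) = 2.802 × 0.258 = 0.723 SD

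The exact t-test version gives 0.736. The value 0.723 serves as the reference effect.

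**Step 2, added variance.** With an SD of 1 among children having the same type of treatment, the mix raises the variance to V = 1 + p(1 − p)k².

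**Step 3, power.** Power = Φ(2.802/√V − 1.960).

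| p | k (SD) | V | Power |
|---|---|---|---|
| any | 0 | 1 | 80.0% |
| 0.3 | 0.5 | 1.0525 | 78.0% |
| 0.5 | 0.5 | 1.0625 | 77.6% |
| 0.3 | 1 | 1.21 | 72.1% |
| 0.5 | 1 | 1.25 | 70.7% |

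The most that stratification or adjustment could recover is therefore about 2 points of power at 0.5 SD and 8 to 9 points at 1 SD.

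**Step 4, chance imbalance is the same quantity.** With 30 per arm, the exact binomial probability that the arms differ by at least 20 percentage points in extraction share is 12% at p = 0.3 and 16% at p = 0.5 (7% and 9% with 40 per arm). Such a difference moves the arm contrast by 0.20 × k = 0.1 to 0.2 SD. But the variance of the arm difference is

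(2/n)[1 + p(1 − p)k²] = 2/n + 2p(1 − p)k²/n,

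and the last term is exactly the contribution of chance imbalance. It is already counted in V and must not be added as a second harm.

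**The case against.** The strongest reply is that randomization balances the treatment mix in expectation. Both arms receive the same range of treatment from a single dentist, and the pre-procedure sample is untouched by that day's treatment. All of this stands. A reader might infer from the imbalance figures that the trial risks a false difference between arms. The documents do not support that: the imbalance is ordinary chance variation, the standard error already contains it, and the type I error is unaffected. Even the 0.1–0.2 SD shift is smaller than the ordinary standard error of the difference, √(2/30) = 0.26 SD.

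A reader might also infer that saliva taken after an extraction contains blood and gives wrong cortisol or amylase values. The article says nothing about blood or its effect on either assay, and handling rules for samples are the kind of detail a condensed article leaves out. Excluding visibly bloody samples would also be a post-randomization exclusion. Completion of treatment is a secondary outcome that acclimatization might change, so such a rule could create selection where none existed.

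On stratification, the objection is partly right. The article does not say that the baseline examination fixes the visit-2 plan. The p-IOSN is recorded at the initial visit, apparently after allocation, and the content of the complexity table is not shown. The fix must therefore be conditional. It is also fair that covariate adjustment may be set out in an unseen analysis plan; what can be judged here is that the stated test is unadjusted and the stated allocation unstratified.

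Finally, the absence of a sample during treatment does not make saliva uninformative about it. How far a sample taken 15 minutes later still reflects anxiety during treatment cannot be determined from the article.

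**Conclusion.** The point holds as a matter of interpretation and precision, not of bias. The mismatch between the hypothesis and the sampling times is plain on the face of the article and needs no assumption. The precision loss is conditional: about 2 points of power if an extraction shifts the marker by 0.5 SD, and 8 to 9 points if it shifts it by 1 SD, with 30–50% of children having an extraction and 30 analysed per arm. Both ranges are assumptions.

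The 80% reference also assumes that the SD behind the sample size applies among children having similar treatment. If that SD already came from a mixed group, 80% is the unadjusted power. Removing the treatment variance would then raise it to Φ(2.802 × √V − 1.960), about 82% at 0.5 SD and 87–88% at 1 SD. The gain is similar in size either way. Pulp therapy is not modelled separately.

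**What to change.** 1. If the baseline examination gives the visit-2 treatment plan before allocation, stratify the block randomization by planned extraction (yes/no) and analyse by that stratum.
2. If it does not, adjust the post-procedure saliva comparison for the treatment plan or treatment complexity score recorded at the initial visit. The value should be fixed before nitrous oxide is given, so that it cannot be affected by allocation.
3. Report the second-visit saliva results as pre-procedure (anticipatory) and post-procedure levels, and align the hypothesis wording, so that neither is presented as direct measurement of anxiety during treatment.
4. At most, note visible blood at collection for a sensitivity analysis. Do not exclude samples on that basis.

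The cost is a second envelope series and a slightly more complex analysis than a plain two-sample test. No change to the sampling times or to treatment is needed.

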**Figure 2 F2:**
[figure not shown]
Modified child dental anxiety scale (Source: SDCEP Oral Health Assessment and Review 2017).

**Table 1 T1:**

Treatment complexity rank score for the pediatric version of the indicator of sedation need (p-IOSN).

**Table 2 T2:**
[figure not shown]
Summary of p-IOSN scoring system modified for children.

Madouh and Tahmassebi^[17]^ validated a pediatric version (p-IOSN). They used two anxiety questionnaires; The facial image scale was used for children under 10 years of age and the faces version of the MCDASf for older children. They also modified the last component of the IOSN which is the “treatment complexity” in order that it would be applicable to children's treatment rather than adults. Each question has five faces ranging from a very happy face to a very sad face and score range of 1 to 5. The total score range is 6 to 30. Children with a score ≥19 will be considered to have severe dental anxiety while those with a score of <19 will be considered to have no to moderate anxiety.

The MCDASf questionnaire will be administered in English. However, Arabic language translated versions will be used when required. The English version was translated into the Arabic language using the forward and backward translation method. The translation was checked by an independent bilingual expert who resolved concerns and discrepancies. To make sure that the translation was effective a back-translation to the English language was done by an independent translator who back-translated the questionnaire and discrepancies in the translation version were resolved.

In addition to the p-IOSN, physiological anxiety related changes will be assessed by measuring the levels of SAA and Cortisol. Salivary samples of 1.5 to 2 ml unstimulated saliva will be collected and analyzed using Expanded Range High Sensitivity Salivary Amylase and Cortisol Enzyme Immunoassay Kit (Bio Medical Scientific Services LLC ISO 9001:2008 Registered Firm. Certificate No.: DQU-12422; Hili Industrial Area, Al Ain, UAE).

Further subjective assessment of behavior and anxiety (Table 3) will be recorded using the numerical FBRS scores (1 to 4 where 1 is extremely uncooperative).^[18]^ Parents and children will be requested to complete a short questionnaire at the end of the treatment visit to measure their acceptance/satisfaction of dental treatment with or without acclimatization visit (Tables 4 and 5).

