### Secondary outcomes

2.2

The following significant outcomes will be classified as evidence of beneficial effect of the acclimatization IHS visit: satisfactory completion of the required dental treatment and children's and parents’ acceptance of dental treatment with or without acclimatization visit. The secondary outcomes are measured by:

(1)Guardian/child quantitative questionnaire.(2)Records from clinical notes

All the parents of children aged 5 to 15 years referred for pediatric specialist treatment in Dubai Dental Hospital in need of treatment under IHS within 6 months’ period will be invited to participate in the study. Inclusion criteria will include: healthy children with American Society of Anesthesiologists (ASA) classification of I or II aged 5 to 15 years in need of dental treatment under IHS, with no learning disabilities and suitable for nitrous oxide/oxygen IHS. UAE and non-UAE nationals’ parents and children will be eligible to participate in the study. Included children should have no previous experience of nitrous IHS. Exclusion criteria will include children with special healthcare needs and/or medically compromised, as well as those with complex medical history (ASA III, ASA IV) or diagnosed with a psychiatric disorder, children who lack communication due to language barrier. Participants will also be excluded if their parents refuse to sign the consent.

A flowchart of the study design is presented in Figure 1.

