(1)the modified child dental anxiety scale (MCDASf) (Fig. 2) using the SDCEP recommended shortened MCDASf questionnaire without the last two questions (on dental sedation and general anesthesia) for all anxious children.^[13]^ The MCDASf has been used widely in many dental behavioral studies.^[14–16]^(2)the treatment complexity rank score (Table 1) records the medical status which is based on the patient's (ASA) classification (Table 2).

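### MCDASf is used at all ages from 5, although the cited p-IOSN validation used another scale under 10; separately, age enters neither the stated randomisation nor the stated tests, which costs precision but not validity

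*Protocol article*

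**What the plan says.** All places are in the protocol article.

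- **Eligibility (section 2.2):** "healthy children with American Society of Anesthesiologists (ASA) classification of I or II aged 5 to 15 years".
- **Trial's anxiety scale (section 2.2, list of p-IOSN components):** "using the SDCEP recommended shortened MCDASf questionnaire without the last two questions (on dental sedation and general anesthesia) for all anxious children". In support, the article cites the guideline that recommends this short form and adds: "The MCDASf has been used widely in many dental behavioral studies".
- **Cited validation of the p-IOSN (text after Table 2):** "The facial image scale was used for children under 10 years of age and the faces version of the MCDASf for older children". The facial image scale is not named anywhere as a measure in this trial.
- **Scoring (same paragraph):** "The total score range is 6 to 30". A single cut-off of 19 separates severe from lesser anxiety, whatever the child's age.
- **Role of the score:** section 2.1 lists an anxiety component of the IOSN among three primary measures, beside the saliva markers and the Frankl scale. Section 2.4.1 speaks of change in self-reported anxiety as the primary outcome measure.
- **Randomisation (text after Figure 1):** "Block randomization with a 1:1 allocation will be performed". No stratification factor is named.
- **Analysis (section 2.8):** mean changes in anxiety with 95% confidence intervals, t-tests or Mann–Whitney tests for quantitative data, and chi-square for categorical data. No age or baseline term is named.

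**The concern.** There are two separate issues, both arising from the wide age range.

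**Instrument.** The article presents the p-IOSN as validated for children and reports that the validated version changed anxiety scale at age 10. It then describes one scale, one range and one cut-off for a sample that starts at 5. A reader may take the cited validation to cover every child, when on the article's own account it covers MCDASf only in the older ones. At stake are how sensitive the score is in younger children, and whether a total of 19 means the same at 6 as at 14.

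**Age balance.** Behaviour ratings, self-report and saliva markers may all vary with age, though the article gives no figures on this. Age is known before randomisation and costs nothing to record. In a trial with 30 or 40 per arm spread over 11 year-bands, leaving age out of both the allocation and the comparison gives away precision.

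**Working it through.** **1. The scale by age**

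| Age | Cited p-IOSN validation | This trial |
|---|---|---|
| 5 to 9 | facial image scale | shortened MCDASf |
| 10 to 15 | MCDASf | shortened MCDASf |

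The mismatch is confined to the first row. Ages 5 to 9 are 5 of the 11 eligible year-bands, 5/11 = 45%. The article does not give the age mix. With an even spread, 30 × 5/11 ≈ 14 children per arm are under 10; at assumed shares of 30% to 70% the number is 9 to 21.

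**2. The plan's own sample size**

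Section 2.3 gives 80% power and 30 patients, without an effect size or SD, so the 30 cannot be reproduced. Reading it as 30 per arm at two-sided 0.05 (an assumption), the implied standardised difference is

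d = (1.960 + 0.842) × √(2/30) = 0.723.

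This is used below only as a reference effect. The text after Figure 1 randomises 30 per group and section 2.3 recruits 40 per group, so both sizes are shown.

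**3. Chance of an age imbalance**

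Let the under-10 counts in the two arms be independent Binomial(n, p), which treats unstratified blocks as simple randomisation with respect to age. A gap of 20 percentage points is 6 children at n = 30 and 8 children at n = 40. Exact probabilities of a gap at least that large:

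| Under-10 share p (assumed) | 30 per arm | 40 per arm |
|---|---|---|
| 30% | 0.120 | 0.067 |
| 45% | 0.153 | 0.092 |
| 50% | 0.155 | 0.093 |
| 60% | 0.147 | 0.086 |
| 70% | 0.120 | 0.067 |

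**4. What leaving age out costs**

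Suppose younger children's scores are shifted by s within-age SDs and p = 5/11. The SD seen by an unadjusted test is √(1 + s² × p(1 − p)), with p(1 − p) = 0.248.

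- s = 0.5: √1.062 = 1.031, so d falls to 0.723/1.031 = 0.702.
- s = 1: √1.248 = 1.117, so d falls to 0.723/1.117 = 0.647.

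Power of the two-sided t-test, from 20,000 simulated trials per setting:

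| Shift s (assumed) | 30 per arm | 40 per arm |
|---|---|---|
| 0 | 79% | 89% |
| 0.5 SD | 76% | 87% |
| 1 SD | 69% | 82% |

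Type I error in the same simulations was 0.047 to 0.050: no inflation.

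A constant age shift cancels in a change from baseline. The loss therefore falls mainly on measures not analysed as change, such as the Frankl score, for which no baseline recording is described.

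**5. If the scale is less sensitive under 10**

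Suppose the effect registered in the under-10s is only 80% or 60% of its size in older children (assumed). Power at 30 per arm then falls from 79% to 71% or 60%. The direction is dilution.

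**The case against.** The strongest reply is that the trial does not rest on the p-IOSN validation alone. Section 2.1 uses one component of the IOSN, not the composite. The article gives that component its own support: a guideline recommendation of the short form and several studies. Their age coverage is not stated and cannot be checked here. The article also reports openly what the validation did and then specifies a single common scale, which is a defensible choice. This stands. A reader might infer that MCDASf is invalid at ages 5 to 9; the documents do not show that. They do not show the reverse either. The preliminary survey (section 2.4.2), in which all 15 children found the form fine to complete, speaks to acceptability and not to validity.

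A reader might also infer that a positive result could be an artefact of the instrument. It could not readily be: both randomised arms receive the same scale, so weakness adds noise or dilutes the effect without favouring either arm.

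On randomisation, unstratified blocks are not an error, and a condensed article may omit a factor. Both points stand, and stratification has no bearing on whether a scale is valid. The imbalance risk is also smaller at the 40 per group of section 2.3 than at 30. What remains is that, as written, the article has no protection against age imbalance at either stage, and the remedy is nearly free.

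A tempting remedy is to add the facial image scale under 10 and let it carry the conclusion there if the two scales disagree. That would choose a primary measure after seeing the data and split a small sample across two scales. It should not be adopted.

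**Conclusion.** The concern holds in a limited form.

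- **Instrument:** for ages 5 to 9 the p-IOSN anxiety component is a modified form of the one whose validation is cited. This should be declared. The likely consequences are reduced sensitivity and a less certain meaning for the cut-off of 19. The cut-off is a classification; the anxiety comparison in section 2.8 is of mean changes.
- **Age balance:** the cost is precision only, with no bias and no inflated type I error. At an assumed half under 10, the chance of a 20-point gap is about 16% at 30 per arm and 9% at 40. The loss of power at 30 per arm is about 3 points for a 0.5 SD age shift and 10 points for 1 SD, and applies mainly to measures without a baseline.

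These sizes rest on an assumed age mix, assumed shifts and a reference effect inferred from the 30, none of which the article supplies. The point merits a change before recruitment because allocation cannot be stratified afterwards.

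**What to change.** 1. Prepare the sealed envelopes as two sets of 1:1 blocks, ages 5 to 9 and ages 10 to 15.
2. In section 2.8, include age in the between-arm comparisons, together with the baseline value where one is collected (anxiety score, saliva markers). Where a rank test is used instead, stratify it by age group.
3. Keep the shortened MCDASf as the single anxiety scale at all ages. State that this modifies the p-IOSN under 10 relative to the cited validation.
4. Report the anxiety result by age stratum as a supportive analysis, without switching to another scale on the basis of the data.

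Cost: a second envelope set, a slightly larger model and a sentence or two of text. No child answers any extra question.
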